**Fig. 1 Fig1:**
[figure not shown]
Study design. Patients are randomly assigned (1:1) to downstream P2Y12 receptor blockers (prasugrel or ticagrelor) or to upstream administration strategy (only ticagrelor). The patients of the downstream arm, who will undergo PCI, will be further randomized (1:1) to downstream prasugrel or downstream ticagrelor before the PCI procedure. All randomizations are blocked by age > 75. Prasugrel is to be administered 60 mg oral bolus then 5 mg daily in subjects > 75 years old or with a weight < 60 kg (**)

### Study drugs administration

Subjects randomized to the upstream strategy arm will receive a loading dose of ticagrelor (180 mg) at admission as soon as possible after randomization. Those in the upstream arm already receiving a chronic therapy with clopidogrel should switch to ticagrelor therapy, starting with a loading dose of 180 mg of ticagrelor (timing from last clopidogrel dose based on clinician’s judgment). Patients randomized to downstream strategy will not receive any loading dose of P2Y12 receptor blockers before coronary angiography. In both treatment arms, adjunctive aspirin will be administered after randomization (100–300 mg oral or i.v. bolus only in naïve patient; maintenance therapy with ≥ 75 mg daily in all patients) as per standard of care. Patients in the downstream arm already on chronic clopidogrel therapy before randomization will continue maintenance clopidogrel 75 mg daily until coronary angiography, but without receiving any loading dose. The timing of myocardial revascularization (PCI or CABG) in this trial will be based upon judgment of the treating physician. For patients requiring PCI, both ad hoc and deferred procedures are allowed. In the downstream arm, it is recommended to administer the P2Y12 inhibitor as soon as possible after the indication to PCI is formulated and before performing PCI. Moreover, in order to facilitate a complete platelet inhibition before PCI is performed, a deferred PCI (> 2 h from P2Y12 administration) may be preferred. Patients requiring PCI in the downstream arm will receive a loading dose of prasugrel 60 mg or ticagrelor 180 mg according to the second randomization. All subjects treated by PCI will be treated with dual antiplatelet therapy including a minimum of 75 mg of aspirin daily and ticagrelor 90 mg b.i.d. or 10 mg of prasugrel daily (according to randomization) for at least 12 months in line with guideline recommendations. In patients > 75 years of age or with a body weight < 60 kg assigned to receive downstream prasugrel, after a 60-mg loading dose, the daily maintenance dose of prasugrel will be 5 mg. After angiography, if the patient does not have an indication for percutaneous or surgical coronary revascularization, and the diagnosis of NSTE-ACS is confirmed, subjects will maintain (upstream arm) or start (downstream arm) DAPT with ticagrelor based on the benefit of ticagrelor [12], but not prasugrel [13], over clopidogrel in medically treated NSTE-ACS patients. If the initial diagnosis of NSTE-ACS is not confirmed or an alternative diagnosis (e.g., myocarditis, tako-tsubo syndrome) is made, the antiplatelet treatment regimen will be defined at the discretion of the treating physician. In patients who have an indication to undergo coronary artery bypass graft (CABG), antiplatelet therapy will be managed according to current ESC guidelines [3, 14]. In the upstream treatment arm, if ticagrelor is discontinued prior to CABG, resumption of a P2Y12 inhibitor should be considered as soon as considered safe. In the downstream arm, a P2Y12 inhibitor should be started after CABG before patient discharge. Patients who are medically managed as well as those undergoing CABG will be not part of the per-treatment evaluable population but will be part of the intention-to-treat population. Related to allowed or prohibited concomitant medications, the use of GPIIb/IIIa inhibitors prior to randomization is not permitted and is an exclusion criterion. After randomization, a GPIIb/IIIa inhibitor can be used according to local practice. Anticoagulant therapy should be started as per local standard of care as soon as diagnosis of NSTE-ACS is made. Anticoagulants may include unfractionated heparin (UFH), fondaparinux, enoxaparin, and—at the time of PCI—bivalirudin (dosing according to latest ESC guidelines) [3].

### Outcome measures

The primary outcome measure (NACE, net adverse cardiac events) is a composite of death from vascular causes (death from cardiovascular causes or cerebrovascular causes and any death without another known cause), non-fatal MI, or non-fatal ischemic stroke, and BARC type 3, 4, and 5 bleeding. The rationale for choosing this composite endpoint was to use a balanced estimate of the effect regarding irreversible organ damage, that is, MI, stroke, plus an estimate of life-threatening and fatal bleedings. Cardiovascular death includes death with a demonstrable CV cause, or any death that is not clearly attributable to a non-CV cause. To be considered a primary endpoint event, an MI must be distinct from the index event. Definitions of spontaneous, PCI-related, and CABG-related MI will be adjudicated based on the third universal definition of myocardial infarction [15]. Stroke is defined as a rapid onset of a new persistent, neurological deficit that lasts for more than 24 h (excluding hemorrhagic stroke). Bleeding includes major, life-threatening, or fatal events according to BARC type 3, 4, and 5 definitions (Table 2). Secondary outcome measures include death from any cause and stent thrombosis. Stent thrombosis is based on Academic Research Consortium definitions and comprises angiographic or pathological confirmation, as well as clinical determination of stent thrombosis [16]. Secondary safety endpoints include BARC type 2, 3, 4, and 5 bleeding; any TIMI major, life-threatening, and minor bleeding; CABG surgery-related TIMI major and minor bleeding; and non-CABG surgery-related TIMI major and minor bleeding [17, 18].

**Table 2 Tab2:** Type 3–5 bleeding criteria according to the BARC classification

Type 3	
Type 3a	
Overt bleeding plus hemoglobin drop of 3 to < 5 g/dL (provided hemoglobin drop is related to bleed)	
Any transfusion with overt bleeding	
Type 3b	
Overt bleeding plus hemoglobin drop ≥ 5 g/dL (provided hemoglobin drop is related to bleed)	
Cardiac tamponade	
Bleeding requiring surgical intervention for control (excluding dental/nasal/skin/hemorrhoid)	
Bleeding requiring intravenous vasoactive agents	
Type 3c	
Intracranial hemorrhage (does not include microbleeds or hemorrhagic transformation, does include intraspinal)	
Subcategories confirmed by autopsy or imaging or lumbar puncture	
Intraocular bleed compromising vision	
Type 4: CABG-related bleeding	
Perioperative intracranial bleeding within 48 h	
Reoperation after closure of sternotomy for the purpose of controlling bleeding	
Transfusion of ≥ 5 U whole blood or packed red blood cells within a 48-h period	
Chest tube output ≥ 2 L within a 24-h period	
Type 5: fatal bleeding	
Type 5a	
Probable fatal bleeding; no autopsy or imaging confirmation but clinically suspicious	
Type 5b	
Definite fatal bleeding; overt bleeding or autopsy or imaging confirmation	

### Primary and secondary endpoints

The primary hypothesis will be tested comparing study groups in terms of the 30-day incidence of the combined efficacy and safety primary endpoint (NACE). A list of safety and efficacy endpoints is reported in Table 3.

**Table 3 Tab3:** Secondary endpoints

Single digit and composite of death from vascular causes (death from cardiovascular causes or cerebrovascular causes and any death without another known cause), MI, stroke, TIA, severe recurrent ischemia, recurrent ischemia, or other arterial thrombotic event	
Death from any cause	
Any stent thrombosis according to the ARC criteria	
Target vessel revascularization (TVR)	
Target lesion revascularization (TLR)	
NACE (net adverse cardiac events) occurred in the period between admission and coronary revascularization defined as a composite of death from vascular causes (death from cardiovascular causes or cerebrovascular causes and any death without another known cause), non-fatal MI, or non-fatal stroke, and BARC type 2, 3, 4, and 5 bleeding	
Compliance to mandated antiplatelet therapy	
BARC type 2, 3, 4, and 5 bleeding (single digit and composite)	
All TIMI major, major life-threatening, and minor bleeding	
All CABG surgery-related TIMI major, minor, and composite of TIMI major or minor bleeding	
Non-CABG surgery-related TIMI major, minor, and composite of TIMI major or minor bleeding	

The primary powered hypotheses include (1) superiority of a downstream administration strategy for P2Y12 receptor blockers over the upstream administration and (2) non-inferiority of prasugrel versus ticagrelor in the PCI group of the downstream strategy arm. The study is powered based on the primary endpoint of incidence at 30 days of the combined primary endpoint. For the comparison of upstream and downstream arms, the intent-to-treat (ITT) population will be considered. The study will provide 80% power to establish the superiority of the downstream strategy on the upstream strategy relative to the primary composite endpoint. These calculations are based on the following assumptions: (1) 8% of patients in downstream arm and 11% of patients in the upstream arm (odds ratio = 1.4) having a primary endpoint event within 30 days from randomization, based on extrapolations of previous data. In particular, in patients with NSTE-ACS pretreated with ticagrelor, the 30-day incidence of a composite efficacy endpoint (comprising cardiovascular death, MI, stroke, TIA, or other arterial thrombotic event) was 6.95%, while the rate of major bleeding was 4.05% [19]. In patients with NSTE-ACS not pretreated with a P2Y12 inhibitor, the observed incidence of the composite efficacy endpoint at 30 days (cardiovascular death, MI, stroke) was 7.2%, while the incidence of non-CABG-related TIMI major bleeds was 0.6% and the incidence of all TIMI major bleeds (CABG-related or non-CABG-related) was 1.5% [8]; (2) the time-to-first event analysis based on a 2-sided log-rank test used at a 2-sided significance level (α) of .05 to assess superiority; (3) a dropout rate of about 10%.

In order to compensate for discrepancies between expected and observed incidence of the primary endpoint, the sample size has been computed using an adaptive approach in three study stages. After each stage, a sample size reassessment will be performed. After having reached the sample size foreseen for each of the three stages, an evaluation using a 95% repeated confidence interval will be used. If the value 0 will be contained in the interval, a sample size reassessment will be performed based on actually observed incidence rates of NACE. Otherwise, data will be passed to the Executive Steering Committee to decide to continue in randomizing patients for the other two analyses or to stop the study. The critical values and the test characteristics of the design were calculated using the Farrington and Manning method [20].

As a second target, non-inferiority of prasugrel versus ticagrelor in the PCI group of the downstream strategy will be considered. Analyses will be performed at the study completion, so no ad interim evaluations are assumed for this study group. Assuming that at least 80% of the patients will have an indication for PCI in the downstream group, based on the above calculations, a sample of about 1000 should be available for randomization in this group. The following assumptions were considered: (i) two-sided non-inferiority test for rejecting the hypothesis that prasugrel and ticagrelor will differ for more than 4% in terms of NACE, (ii) an overall confidence bounds in non-inferiority testing at 0.95 level (α = 0.025), (iii) an overall sample size of 1000 patients (500 prasugrel + 500 ticagrelor), and (iv) an anticipated incidence rate of 5% in downstream ticagrelor and 8.5% in downstream prasugrel and a true difference in incidence rates of 1% between treatment groups [1, 2, 8]. This approach combines the target clinically relevant maximal difference between treatments of 1% with previous information on a relevant distance in terms of effects between treatments (8.5% versus 5%) [21]. This design corresponds to the Palesch and Tilley “futility design” [22, 23], aimed at screening out-of-target therapeutic approaches, in particular in the cardiovascular field [23]. Power calculations have been made using the R-system [24] and gsDesign libraries [25]. For time-to-event variables, survival curves will be constructed using Kaplan-Meier estimates, and log-rank test results will be displayed for descriptive purposes only. Demographics, procedural, imaging, laboratory, exercise testing, quality of life, and diary related data that are not part of the list of endpoints will be displayed for descriptive purposes only.

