**Study design:**

DUBIUS is a phase 4, multicenter, parallel-group, double randomized study conducted in NSTE-ACS patients designed to compare a pretreatment strategy (including only ticagrelor) versus a downstream strategy (including prasugrel or ticagrelor) and to compare downstream prasugrel with downstream ticagrelor. A total of 2520 patients will be randomly assigned to pretreatment with ticagrelor or to no pretreatment. The PCI group of the downstream arm will be further randomized to receive prasugrel or ticagrelor. The two primary hypotheses are that the downstream strategy is superior to the upstream strategy and that downstream ticagrelor is non-inferior to downstream prasugrel, both measured by the incidence of a composite efficacy and safety endpoint of death from vascular causes, non-fatal MI, or non-fatal stroke, and Bleeding Academic Research Consortium (BARC) type 3, 4, and 5 bleedings.

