### Consenting and randomization

Investigators of each participating site will be cardiologists or cardiology fellows and will assess eligibility, obtain patient informed consent prior to performing any study procedures, enroll eligible patients, and assign patients to interventions. The informed consent form is reported in Additional file 2. All subjects enrolled will be randomly assigned in a parallel 1:1 fashion to downstream administration strategy of P2Y12 receptor blockers (prasugrel or ticagrelor) or to an upstream administration strategy (only ticagrelor) (Fig. 1). The randomization to the upstream or the downstream arm should occur as soon as possible after admission. The patients of the downstream arm, who will undergo PCI, will be further randomized in a 1:1 fashion to downstream prasugrel versus downstream ticagrelor at the time of PCI. The second randomization (prasugrel versus ticagrelor) will occur after coronary angiography and before the PCI procedure. The allocation sequence of patients into study groups will be computer-generated by a central system located at the coordinating center. Allocation sequence will be concealed to investigators. Investigators will obtain the randomization information of patients enrolled at their site by a dedicated online system (https://redcap.dctv.unipd.it). Enrolled subjects and investigators will not be blinded to study treatments, so unblinding will not occur. In order to avoid imbalances between groups with respect to age, all randomizations will be blocked by age > 75 years or ≤ 75 years. On the consent form, participants will be asked if they agree to use of their data should they choose to withdraw from the trial. Participants will also be asked for permission for the research team to share relevant data with people from the Universities taking part in the research or from regulatory authorities, where relevant. This trial does not involve collecting biological specimens for storage. A centralized online system will be used for randomization. Once randomized, the subjects are considered enrolled in the study and analyzed as the intent-to-treat (ITT) population.

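### The stated 80% power does not follow from the stated inputs: as a fixed trial of 2520 patients, 8% versus 11% at two-sided 0.05 gives about 73%, or about 68% after 10% dropout

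*Protocol article*

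**What the plan says.** The Abstract (Study design) gives the size: "A total of 2520 patients will be randomly assigned to pretreatment with ticagrelor or to no pretreatment". Consenting and randomization gives the allocation: "All subjects enrolled will be randomly assigned in a parallel 1:1 fashion to downstream administration strategy".

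The section Primary and secondary endpoints gives the rest:

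- Power: "The study will provide 80% power to establish the superiority of the downstream strategy on the upstream strategy relative to the primary composite endpoint".
- Event rates: "8% of patients in downstream arm and 11% of patients in the upstream arm", counted as "having a primary endpoint event within 30 days from randomization".
- Test: "2-sided log-rank test used at a 2-sided significance level" of 0.05.
- Loss: "a dropout rate of about 10" per cent.

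The same section adds that "the sample size has been computed using an adaptive approach in three study stages". After each stage a 95% repeated confidence interval is evaluated, and the size is reassessed from the observed event rates if the interval contains zero. The purpose given is to compensate for a mismatch between expected and observed incidence. No boundary shape, stage sizes or total above 2520 are printed. The count of about 1000 PCI patients for the second hypothesis agrees with 2520 as the planned total, since 80% of 1260 is 1008.

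**The concern.** Every quantity needed to check the power is printed, so the claim can be tested without the full protocol. Event rates of 8% and 11% are close together for a trial of this size, and 80% looks high once a tenth of the patients are lost.

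The figure matters because this is the first primary hypothesis. If the planned difference is real, readers will take the chance of missing it to be 20%. On the stated inputs, for a fixed trial of this size, it is about 27% with complete follow-up and about 32% after dropout. A neutral result would then be given more weight as evidence against a 3-point benefit than the trial can support.

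**Working it through.** **Inputs.** N = 2520, so 1260 per arm. After 10% loss, 2520 × 0.9 = 2268, so 1134 per arm. p1 = 0.08 and p2 = 0.11, with difference 0.03 and mean 0.095. Two-sided α = 0.05, so z = 1.960. For 80% power, z = 0.8416.

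**Attempt to reproduce the 80% (two proportions, pooled variance under the null).**

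Power = Φ{ [0.03·√n − 1.960·√(2·0.095·0.905)] / √(0.08·0.92 + 0.11·0.89) }

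The two fixed terms are 1.960 × 0.4147 = 0.8128 and √0.1715 = 0.4141.

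- n = 1260: (1.0649 − 0.8128)/0.4141 = 0.609, so power is **72.9%**.
- n = 1134: (1.0102 − 0.8128)/0.4141 = 0.477, so power is **68.3%**.

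**Size needed for 80%.**

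n per arm = (0.8128 + 0.8416 × 0.4141)² / 0.03² = 1,498.4, rounded up to 1,499. That is 2,998 evaluable patients. Dividing by 0.9 gives about 3,330 randomised.

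**Log-rank version (Schoenfeld).** HR = ln(0.89)/ln(0.92) = 1.398, and ln HR = 0.3348. Expected events are 2520 × 0.095 = 239.4, or 2268 × 0.095 = 215.5.

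Power = Φ(½·√events × 0.3348 − 1.960)

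- 239.4 events: Φ(0.630) = **73.6%**.
- 215.5 events: Φ(0.497) = **69.0%**.
- For 80%: 4 × (1.960 + 0.8416)² / 0.3348² gives 281 events. That is 281/0.095 = 2,958 evaluable, or about 3,287 randomised.

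**Could another convention give 80%?**

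| Variant | No dropout | 10% dropout |
|---|---|---|
| Pooled two proportions, two-sided | 72.9% | 68.3% |
| Unpooled, two-sided | 73.0% | 68.4% |
| Schoenfeld, HR 1.398 | 73.6% | 69.0% |
| Freedman, HR 1.398 | 72.8% | 68.2% |
| Schoenfeld, HR 1.4 (the printed odds ratio) | 74.0% | 69.5% |
| Schoenfeld, exact odds ratio 1.42 used as HR | 77.6% | 73.3% |
| Pooled two proportions, one-sided 0.05 | 82.2% | 78.6% |

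No two-sided variant reaches 80%. If dropouts contribute half their information, the pooled figure is 70.7%.

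**Effect of the three looks at a fixed size.** The article prints no boundary, so this is an assumption: three equal stages, simulated. O'Brien-Fleming boundaries give 72.2% (2520) and 67.5% (2268). Pocock boundaries give 65.5% and 60.8%. The penalty is therefore under one point for the first shape and about seven points for the second.

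**Difference detectable with 80% power, fixed design, downstream at 8%.** At 1260 per arm it is 3.3 points (8.0% versus 11.3%). At 1134 per arm it is 3.5 points (8.0% versus 11.5%).

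**The case against.** The strongest reply is that 2520 is not a fixed size. The design is adaptive, and reassessment can add patients and so raise power. This is true in principle. As an illustration, assume three equal stages, O'Brien-Fleming boundaries, inverse-normal weighting, and a last stage that may double after the second look. Power at 8% versus 11% is then about 81% without dropout and about 77% starting from 2268. A reader might infer from the calculation above that the whole adaptive design delivers only 68%. The article does not support that, because stage sizes and any cap may stand in the full protocol. What the reply does not do is justify the printed claim. Reassessment is presented as a remedy for event rates that differ from those planned, no total above 2520 is given, and the 80% is stated for exactly the planned rates.

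A second reply is that an intention-to-treat analysis with complete 30-day follow-up loses nobody. Power is then about 73%, which is still short, and the article itself lists dropout among the assumptions.

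A third is that a one-sided test may lie behind the figure. The numbers fit (82% and 79%), but this is only an inference, and the article calls the test two-sided.

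A reader might also infer that the downstream rate should be 8.7% (7.2% plus the 1.5% for all TIMI major bleeds), which would cut power below 50%. The documents do not support that step. The rates are described as extrapolations, not sums. Adding components counts patients with both events twice, and TIMI major bleeding is not BARC 3 to 5. The upstream source figure also includes TIA and other arterial events that the primary endpoint leaves out, so changing one arm alone is not a like-for-like comparison.

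**Conclusion.** Wrong as written. On the article's own inputs, a fixed trial of 2520 patients has about 73% power with complete follow-up and about 68% after 10% dropout (log-rank about 74% and 69%), not 80%. The planned size is about 24% below the roughly 3,330 that these inputs require (2520/3,330 = 0.76).

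The result rests on 1:1 allocation, the planned rates being true, and, for the lower figure, dropouts contributing no information. The figures are before the sequential penalty, whose size depends on an unstated boundary, and before any increase from reassessment. They describe the fixed 2520-patient trial and not the operating characteristics of the full adaptive plan.

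**What to change.** Keep 2520 as the planned size and correct the power statement in Primary and secondary endpoints. Either of these would do:

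- *About 73% power with complete follow-up and about 68% with 10% dropout, for 8% versus 11% at two-sided 0.05, before any sample size reassessment and before the sequential penalty.*
- *80% power for a difference of about 3.3 points (complete follow-up) to 3.5 points (10% dropout), fixed-design value.*

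The cost is a text amendment and a less favourable stated power. The correction adds no patients and leaves the test, the endpoint and the reassessment procedure as they are.

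### The 11% and 8% planning rates appear to rest on event definitions that differ from each other and from NACE, and even as stated they give about 74% power at 2520 patients, not 80%

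*Protocol article*

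**What the plan says.** All references are to the Protocol article.

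- **Power claim** (Primary and secondary endpoints): "The study will provide 80% power to establish the superiority of the downstream strategy on the upstream strategy". The stated inputs are "8% of patients in downstream arm and 11% of patients in the upstream arm" within 30 days, a "2-sided log-rank test used at a 2-sided significance level (α) of .05 to assess superiority", and "a dropout rate of about 10" per cent. The abstract gives the size: "A total of 2520 patients will be randomly assigned to pretreatment with ticagrelor or to no pretreatment".
- **Upstream source figures** (same section): a 30-day efficacy composite of 6.95%, described as "comprising cardiovascular death, MI, stroke, TIA, or other arterial thrombotic event", and major bleeding of 4.05% with no scale named.
- **Downstream source figures** (same section): 7.2% for cardiovascular death, MI and stroke. Two bleeding figures follow: 0.6% for non-CABG TIMI major bleeding, and "the incidence of all TIMI major bleeds (CABG-related or non-CABG-related) was 1.5" per cent.
- **The trial's own endpoint** (Outcome measures): vascular death, non-fatal MI, "non-fatal ischemic stroke, and BARC type 3, 4, and 5 bleeding". Table 2 defines BARC type 4 as CABG-related bleeding.

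The planning rates are described only as extrapolated from previous data. The article does not say how the components were combined.

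**The concern.** The 11% and 8% are presented as rates of the primary endpoint, but the figures offered in support are not rates of that endpoint, and the two arms' sources do not share a definition. The upstream efficacy composite is broader than NACE. The downstream bleeding figure that best explains the 8% leaves out CABG-related bleeding, which NACE counts, and CABG patients stay in the intention-to-treat population used for this comparison (Study drugs administration).

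On efficacy the quoted figures run slightly against downstream, even though the upstream composite is the broader one. The planned advantage therefore depends wholly on a contrast between two bleeding rates that the article does not show to be on the same scale.

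At stake is the power statement for the first primary hypothesis. A null result at 2520 patients would be read against a claimed 80% chance of detecting the benefit. That chance is lower even at the stated rates, and it is sensitive to how the rates were built.

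**Working it through.** **1. Where the rates seem to come from (percentage points).**

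- Upstream: 6.95 + 4.05 = 11.00, an exact match to 11%.
- Downstream, non-CABG bleeding: 7.2 + 0.6 = 7.8, which rounds to 8.
- Downstream, all TIMI major bleeding: 7.2 + 1.5 = 8.7, which does not.
- Efficacy difference, upstream minus downstream: 6.95 − 7.2 = −0.25.
- Bleeding difference: 4.05 − 0.6 = 3.45. Net: 3.45 − 0.25 = 3.20, against the planned 3.

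**2. Method.** Log-rank power by Schoenfeld's formula, two-sided 0.05, 1:1 allocation:

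- HR = ln(1 − p_down) / ln(1 − p_up)
- events d = n × (p_up + p_down), with n per arm
- power = Φ(√(d/4) × |ln HR| − 1.96)

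n is 2520/2 = 1260, or 1260 × 0.9 = 1134 after 10% dropout. The article does not make clear whether 2520 already allows for dropout, so both are shown.

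**3. The plan's own figure, 11% v 8%.**

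- HR = ln(0.92)/ln(0.89) = 0.7155, so |ln HR| = 0.3348.
- n = 1260: d = 1260 × 0.19 = 239.4; power = Φ(7.736 × 0.3348 − 1.96) = Φ(0.63) = 73.6%.
- n = 1134: d = 215.5; power = 69.0%.
- A pooled two-proportion test gives 72.9% and 68.3%.

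The stated 80% is not reproduced. By the two-proportion method it would need 2998 patients, or 3332 with dropout. The nearest match on a two-sided test is 11% v the unrounded 7.8% with no dropout, at 79.4%. That departs from both the stated 8% and the stated dropout.

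**4. Sensitivity to the definitions.**

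| Upstream v downstream | Basis | Power, n = 1260 | Power, n = 1134 |
|---|---|---|---|
| 11% v 8% | as stated | 74% | 69% |
| 11% v 8.7% | 1.5% used downstream, upstream unchanged | 49% | 45% |
| 10.7% v 8.6% | as above, overlap removed assuming independence | 44% | 41% |
| 11.9% v 8.7% | 0.9 points (1.5 − 0.6) added to 11% and 7.8%; assumption | 76% | 71% |
| 10% v 8.7% | lower upstream rate; assumption | 20% | 19% |
| 12% v 8.7% | higher upstream rate; assumption | 78% | 74% |

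The overlap row uses a + b − ab: 0.0695 + 0.0405 − 0.0695 × 0.0405 = 0.107, and 0.072 + 0.015 − 0.072 × 0.015 = 0.086.

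**5. Detectable difference.** Solving the same formula for 80% power with 11% upstream gives about 7.8% downstream at n = 1260 and 7.6% at n = 1134.

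**The case against.** **The 49% carries a mismatch of its own.** It adds CABG bleeding to one arm only. If the 4.05% excludes CABG bleeding, the same addition belongs upstream, and power returns to about 76%. This stands. A reader might infer that the trial's real power is 49%, or that the endpoint definitions alone take it from 80% to 49%. The documents support neither. The CABG content of the 4.05% is not stated. About 6 of the lost points (11 after dropout) are already missing at 11% v 8%, before any question of definition arises.

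**Some steps are inferred.** The article never says the components were summed, and 8% lies between 7.8% and 8.7%. With no scale named for the 4.05%, it cannot be said that it was not BARC 3–5, nor that patients with both event types were counted twice. This also stands: what can be said is that comparability is not shown. The exact match at 11.00% makes summation the likely route, but not a certain one.

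**The design is adaptive.** The plan reassesses sample size over three stages using observed NACE rates, to compensate for planning rates that prove wrong. This may soften the consequence, since 2520 need not be final. It does not make the stated 80% correct for 2520 patients at the stated rates.

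**Conclusion.** The point holds in two parts.

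- **Certain from the stated inputs:** at 11% v 8%, two-sided 0.05, 2520 patients give about 74% log-rank power, or 69% after 10% dropout, and not 80%.
- **Well supported but partly inferred:** the two rates appear to come from sources whose definitions differ from each other and from NACE. The whole 3-point benefit then rests on bleeding rates not shown to be comparable.

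The power on a consistent NACE definition cannot be fixed from the article. With 8.7% downstream it runs from about 20% to 78% as the upstream rate goes from 10% to 12%; 49% is the value at 11%. Removing TIA and other arterial events would lower the upstream rate, while adding CABG bleeding, if it is absent, would raise it. TIMI major bleeding is not BARC 3–5, so 8.7% is only the closest downstream figure the article offers. All these values apply to a fixed 2520 and ignore the staged reassessment.

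**What to change.** In Primary and secondary endpoints:

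1. Derive both rates on one stated definition that matches NACE, with CABG-related bleeding included in both arms. State the bleeding scale of each source.
2. State the allowance made for TIA and other arterial thrombotic events in the upstream figure, and for patients with both an ischaemic and a bleeding event.
3. Replace the 80% with the power that 2520 patients give at 11% v 8% (about 74%, or 69% after dropout), plus a sensitivity range that varies both arms' rates. Alternatively, state the difference detectable with 80% power: with 11% upstream, about 7.8% downstream, or 7.6% after dropout. Say whether 2520 already includes the dropout allowance.

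Steps 1 and 2 need the source publications, because the article's figures do not allow TIA to be removed or a BARC 3–5 rate to be built. The change is to the text only and requires no extra patients. The cost is a less favourable stated power.
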